## **11. STATISTICAL METHODS**

### **11.1 Hypothesis**

The primary aim of the randomized controlled trial is to test the efficacy of the brief motivational intervention model developed in the first part of this project by comparing it to a control condition receiving a minimal intervention (structured brief advice).

The Null hypothesis is that both interventions have comparable effects in reducing

- a) the number of Heavy drinking days (HDD, i.e. the number of days with 6 standard drinks or more, equivalent to 60 grams of pure alcohol or more, over the last month), and
- b) alcohol-related problems as measured by the Short Inventory of Problems (SIP) total score, over 3 the follow-up times (3-, 6-, and 12-month after intervention).

The Alternative hypothesis is that participants in the Brief motivational intervention group (experimental condition – intervention model developed in the first phase of the project) reduce

- a) the number of Heavy drinking days (HDD, i.e. the number of days with 6 standard drinks or more, equivalent to 60 grams of pure alcohol or more, over the last month), and
- b) alcohol-related problems as measured by the Short Inventory of Problems (SIP) total score, more than participants in the control group (structured brief advice) over the 3 follow-up times (3-, 6-, and 12-month after intervention).

### **11.2 Determination of Sample Size**

Based on studies with similar population (intoxicated young adults), setting (ER), and intervention (MI or BMI), we anticipate small to medium effects in favour of participants in the BMI group on alcohol use measures and alcohol-related problems (Monti et al. 1999; Smith et al. 2003; Spirito et al. 2004; Sommers et al. 2006; Monti et al. 2007).

Using a program for power analysis in longitudinal design (Rochon, 1998) a sample of N=172 patients per group (with attrition of 5-20% over follow-ups) will be required to detect small/medium effect sizes (.25), with power at .8, alpha at .05, and moderate autocorrelation dampening in GEE models for the primary outcomes.

The total sample size will thus be of 344 participants (1:1 ratio).

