#### 11.4.2 Primary Analysis

We will test intervention effects over time by comparing groups on the 2 primary and 6 secondary outcomes. For repeated measures, analyses will be conducted using generalized estimating equations (GEE) with robust standard error estimate (Liang and Zeger, 1986). This approach offers an extension of regression analysis to the case of correlated observations over time; it allows for specification of the assumed correlation structure as well as the appropriate link functions to handle dependent variables with a normal distribution, dichotomous outcomes, count data (Poisson), and over-dispersed count data (negative binomial). Models will all be adjusted for the baseline AUDIT score. For outcomes measured at 12-month only, analyses will be conducted using baseline adjusted regression models.

Analyses will be performed at the completion of data collection.

Analyses will be performed by the study PI ([name]), in collaboration with research collaborator [name], and consulting from study co-Is ([name], [name], [name]) and international collaborators ([name], [name]).

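### Two primary outcomes share one alpha of .05 and one power of .8 with no success rule, so the protocol does not say which claim those figures cover

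*Protocol*

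**What the plan says.** Section 5.1 names two primary outcomes, the number of heavy drinking days in the last month and the SIP total score, each assessed at 3, 6 and 12 months. It does not rank them.

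Section 11.1 gives one null and one alternative hypothesis. Each lists the two outcomes as a) and b), joined by *and*. The alternative ends with "alcohol-related problems as measured by the Short Inventory of Problems (SIP) total score, more than participants in the control group (structured brief advice").

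Section 11.2 gives one effect size (.25), one power and one alpha. The trial is planned "with power at .8, alpha at .05, and moderate autocorrelation dampening in GEE models for the primary outcomes". Allowing for 5–20% loss during follow-up, the calculation arrives at 172 per arm, or 344 in all.

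Section 11.4.2 plans to test intervention effects by "comparing groups on the 2 primary and 6 secondary outcomes". Section 11.4.4 rules out interim analyses, so no alpha is spent elsewhere.

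No section orders the two primary outcomes, divides alpha between them, says whether one or both must be significant, or gives a joint power.

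**The concern.** The hypothesis is worded for a pair of outcomes, while the sample size appears to be worked out for one. The figures .8 and .05 then carry over to the trial-level claim only under a rule that the protocol does not state. If the claim needs both outcomes, its power is below .8. If it needs only one, the chance of at least one false positive is above .05.

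The practical case is a split result, with one primary outcome significant and the other not. The protocol gives no basis for calling that trial positive or negative, and the decision could then be taken after the results are known. This matters more here because section 6.2.2 says that data analysts will not be blinded, and section 11.4.2 has the principal investigator performing the analysis.

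**Working it through.** **Inputs from the protocol.** Effect size .25, 172 per arm, power .8, alpha .05, attrition 5–20% (section 11.2); three follow-ups for the primary outcomes (5.1); two primary outcomes (5.1, 11.4.2).

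**Assumptions, not in the protocol.** Two-sided tests (sidedness is not stated). Within-participant correlation ρ = .5 as a reading of *moderate*, with damping exponent 0, .5 or 1 on equally indexed visits. Correlation r between the HDD and SIP test statistics from 0 to .8.

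**Step 1. Does 172 fit a single outcome?** Per arm, n = 2V(z.975 + z.8)²/.25², where V is the variance factor for the time-averaged difference.
- One time point, V = 1: 2 × (1.960 + 0.842)²/.0625 = 251.2, so 252 per arm.
- Three visits, constant correlation .5: V = (1 + 2 × .5)/3 = .667, so n = 251.2 × .667 = 167.4, or 168 with complete data. With attrition rising from 5% to 20% over the visits this becomes 183.
- With damping exponents .5 and 1, the figures after attrition are 176 and 167.

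The stated 172 cannot be reproduced exactly, because the correlation is not given. It does lie within this range of 167 to 183. So it is consistent with one outcome tested at two-sided .05 with 80% power, and nothing here shows it to be wrong.

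**Step 2. Operating characteristics for two outcomes.** Each test statistic has mean μ = 1.960 + 0.842 = 2.80 under the planned effect and mean 0 under the null. The pair is bivariate normal with correlation r.
- Both significant: P(Z₁ > 1.96 and Z₂ > 1.96) at mean μ. At r = 0 this is .8² = .64.
- Exactly one significant: .8 + .8 − 2 × P(both). At r = 0 this is 1.6 − 1.28 = .32.
- At least one false positive, two-sided: 1 − P(|Z₁| and |Z₂| both ≤ 1.96) at mean 0. At r = 0 this is 1 − .95² = .0975.
- At least one false positive in favour of the motivational intervention: the same, counting the upper tail only. At r = 0 this is 1 − .975² = .0494.

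| r | Power for both | Exactly one significant | Familywise error, two-sided | Error in favour only |
|---|---|---|---|---|
| 0 | .640 | .320 | .0975 | .049 |
| .3 | .666 | .268 | .0951 | .048 |
| .5 | .687 | .226 | .0907 | .045 |
| .7 | .713 | .174 | .0835 | .042 |
| .8 | .729 | .142 | .0781 | .039 |

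**Step 3. For scale.** A joint power of .80 would need about 226, 215 or 201 per arm at r = 0, .5 or .8, against the planned 172. Splitting alpha equally (.025 each) at 172 per arm gives a power of .71 per outcome.

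**The case against.** The strongest objection is that a decision rule for two primary outcomes is often left to the statistical analysis plan, which is not at hand. Section 11.2 also never claims a joint power of .8 or a familywise error of .05. Read per outcome, both figures are true. A fixed testing order would keep error at .05 and power at .80 for the first outcome. All of that stands, and it limits the point. What remains is that 11.1 states a hypothesis about HDD and SIP together, and no later document can make .80 the power for that pair at 172 per arm unless the two statistics are perfectly correlated. Section 2.3 also lists changes to endpoints and to the form of statistical analysis among significant changes, so the rule belongs in the protocol.

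Four stronger readings are tempting and are not supported:
- **That the trial fails on both power and error.** The two exclude each other. If both outcomes are required, testing each at .05 is correct and nothing is inflated. If either suffices, the power to find something is not reduced.
- **That the chance of a false claim for the intervention is near 10%.** The .078 to .0975 counts both directions. Errors in favour of the intervention alone are about .039 to .049 with two-sided tests.
- **That the *and* in 11.1 is already a both-required rule.** The null is joined by the same word, so it may be no more than a list.
- **That 344 participants are too few.** The size is workable under a stated rule.

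Nor do the documents show that HDD and SIP tend to diverge. The 14% to 32% for a split result follows from sampling variation alone.

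**Conclusion.** The point holds as a mismatch between the hypothesis, the sample-size statement and the analysis. The figures .05 and .8 fit each outcome separately, and the protocol does not tie them to a rule for the pair. For r between 0 and .8, power is about .64 to .73 if both outcomes are required, or two-sided familywise error is about .078 to .0975 if either suffices. A split result would occur in about 14% to 32% of trials in which both effects are exactly as planned, and its meaning is undefined.

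This rests on three things that the protocol does not state: that .8 applies per outcome (an inference from the single alpha, power and effect size, with which 172 is consistent), that tests are two-sided, and the range for r. It should be fixed. It does not invalidate the design.

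**What to change.** Before outcome data are seen, state one success rule in 11.1 and repeat it in 11.4.2. In 11.2, say which claim the .80 covers. Keep N=344. Two options are open to the sponsor:

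1. **Both required.** Each outcome is tested at two-sided .05 and success means both are significant. Label .80 as the power per outcome, and disclose a joint power of about .64 to .73 with its assumed correlation. This matches the *and* wording of 11.1.
2. **An alpha-controlling procedure.** An example is a fixed sequence at two-sided .05 in an order that the sponsor confirms, such as HDD and then SIP. The protocol lists HDD first but does not rank it, so the order is the sponsor's decision. The .80 then applies to the first outcome only, and 11.1 should be reworded so that success no longer reads as needing both.

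The change is to wording in three sections. The first option costs a less favourable stated power. The second means that no confirmatory claim can be made on the second outcome if the first fails.

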### **11.3 Statistical criteria of termination of trial**

Not applicable.

### **11.4 Planned Analyses**

#### **11.4.1 Datasets to be analysed, analysis populations**

Primary analyses of the efficacy of the intervention (randomized controlled trial) will use all data available from all participants included in the trial. Analysis will be performed in an intention to treat paradigm (i.e. participants having left the ER without finishing the intervention, and/or not receiving intervention booster sessions will be analyzed in the intervention group).

Secondary analysis of mechanisms (Aim 3 of the project) will use data available for the corresponding analyses (e.g. participants with audio-recorded sessions for psycholinguistic coding; randomly selected sub-sample for qualitative analyses). Also, moderation analyses are designed as part of the mechanism analyses. For these, the relative efficacy of the BMI will be tested as an interaction with participants' characteristics, such as age, gender, alcohol problems severity, readiness to change, or personality traits.

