### 5.3 Other Outcomes of Interest

Additional measures for intervention mechanisms study will also be assessed at different time points (see table below) in order to conduct moderation and mediation analysis (see chapter 11.4.3 Secondary analysis).

|                                                                    | Baseline | Post-session | 1-month | 3-month | 6-month | 12-month |
|--------------------------------------------------------------------|----------|--------------|---------|---------|---------|----------|
| Alcohol use disorder severity (Babor et al. , 2001)         | x        |              |         |         |         |          |
| Readiness Rulers (Rollnick, 1998)                                  | x        | x            |         |         |         |          |
| Actual-ideal discrepancy (McNally et al. , 2005)            | x        | x            | x       | x       | x       |          |
| Alcohol-related expectancies (Ham et al. , 2005)            | x        |              | x       | x       | x       |          |
| Depression/Anxiety (Kroenke et al. , 2009)                  | x        |              |         |         |         |          |
| Attribution of injury to alcohol (Longabaugh et al. , 1995) | x        |              |         |         |         |          |
| Severity of ER admission and diagnosis (medical records)           | x        |              |         |         |         |          |
| Quality of life (de Boer et al. , 2004)                     | x        |              | x       | x       | x       |          |
| Patient rating of the treatment (Lee et al. , 2007)         |          | x            |         |         |         |          |
| Working alliance inventory (Horvath and Greenberg, 1989)           |          | x            |         |         |         |          |
| Trait reactance (Shen and Dillard, 2005)                           |          |              | x       |         |         |          |

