### 7.2 Recruitment and screening

The study will be conducted at the Lausanne University Hospital ER, Switzerland. According to administrative data over 7 weeks randomly selected between November 2012 and March 2013, intoxicated young adults are admitted almost only in the later part of the week. For economic reasons, we will limit study recruitment in the ER to Thursday to Sunday mornings from 7am to 2pm, covering 85% of eligible patients. Patients meeting inclusion criterion and having been treated outside this time frame will be contacted by phone and proposed to come to Lausanne University Hospital Alcohol Treatment Center to participate in the study.

All consecutive patients between the age of 18 and 35, admitted in the ER (for any cause) and having alcohol intoxication (>0.5 gram/liter BAC or clinical indication of alcohol intoxication) will be contacted by a member of the research staff during study period. Patients meeting inclusion criterion but being too intoxicated will be contacted by research staff once they have sobered up.

First, research staff will conduct a screening process to evaluate inclusion and exclusion criterion (see Chapter 7.1 above). In case only exclusion criteria e) is not fulfilled (i.e. psychiatric or medical contra-indications preventing patients understanding informed consent, fulfilling questionnaires, and participating in the intervention; evaluated using an adaptation of the University of California, San Diego Brief Assessment of Capacity to Consent – UBACC; McCormack et al. 2014), research staff will come back later to re-assess UBACC and complete further study process if the UBACC score is positive.

For those included, baseline assessment questionnaire will then be conducted in the ER, in a separate space providing confidentiality and using a tablet-based electronic questionnaire administered by a research clinician. The questionnaire will be short (about 5 minutes), first as patients might be hung-over as a result of alcohol intoxication, and second to reduce reactivity to alcohol assessment which has been shown as a source of bias (Gallen, 1974; McCambridge & Kypri, 2011).

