### **9.3.2 Month 1, by phone**

- Alcohol use (30-day timeline follow-back)
- Readiness to change questionnaire
- Alcohol Abstinence Self-efficacy Scale – Reduced drinking
- Alcohol-related expectancies
- Actual-ideal drinking discrepancy
- Substance use
- Quality of life
- Alcohol treatment
- Trait reactance (Hong) – 14 items
- Alcohol treatment

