#### 11.4.3 Secondary Analyses

Analyses of intervention mechanisms (Aim 3 of the project) will include the following analyses:

*Moderation.* Separate GEE models will test the main effect of treatment on outcome, followed by the effect of each moderator variable, and then the interaction of the treatment with each moderator variable.

*Mediation.* To examine mediators of the main effect of the MI intervention on outcomes, we will use Model 4 of the PROCESS algorithm developed by Hayes (2013). Here, regression analyses are used to test path *a* (the effect of the treatment condition on the hypothesized mediators) and path *b* (the effect of each respective mediator on outcomes, while also controlling for the treatment effect on outcomes). Then indirect effects are estimated using bootstrapping, a nonparametric resampling procedure that does not impose the assumption of normality of the sampling distribution (Hayes, 2013; Preacher & Hayes, 2008).

*Moderated mediation* aims at measuring if the effect is transmitted through the designated mediators only under specific circumstances. Several models of the PROCESS algorithm (e.g. 7, 9, 58) allow calculation of moderated mediation (also known as conditional indirect effects) (Hayes, 2013) (Hayes, 2013). These different models specify which path (*a*, *b*, both) of the mediated relationship are moderated. As in mediation, bootstrapping is used to derive conditional indirect effects.

*Qualitative analyses.* In addition to the quantitative analysis of interventions' mechanisms exposed above, we will use qualitative techniques to analyze intervention and follow-ups feedback. A random sub-sample of 20 BA and 20 MI sessions will be transcribed and analyzed using thematic analysis and recursive abstraction techniques (Maxwell, 2005). In addition, semi-structured interviews will be conducted after the 1-month and 12-month follow-up questionnaire with another randomly selected 10 patients having received BA and 10 MI sessions. Topics addressed will be qualitative assessment of potential short-/long-term changes experienced during the follow-up period and their relation or not with the intervention received.

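### The only personality-trait scale, trait reactance, is first measured at month 1, so its interaction with treatment cannot be read as baseline effect moderation

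*Protocol*

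**What the plan says.** Protocol 11.4.1 makes moderation part of the mechanism analyses: the relative efficacy of the brief motivational intervention (BMI) is tested as an interaction with characteristics "such as age, gender, alcohol problems severity, readiness to change, or personality traits". Section 11.4.3 sets a modelling order that ends with the product term of arm and moderator; it begins: "Separate GEE models will test the main effect of treatment on outcome, followed by the effect of each moderator variable". The conceptual model later in 11.4.3 has moderators, patient personality among them, acting on therapist and patient behaviour in the session.

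Section 5.3 introduces its table of measures as collected "in order to conduct moderation and mediation analysis", without saying which scale serves which purpose. The one personality-trait scale in that table is marked under 1-month only. In the visit lists, "Trait reactance" (14 items) appears in 9.3.2, the month-1 phone interview, and at no other visit.

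The Day-1 questionnaire (9.3.1 E) comes before randomisation (9.3.1 F). It includes socio-demographics, the AUDIT and the Readiness Rulers, but no personality scale. Section 7.2 explains its brevity: "The questionnaire will be short (about 5 minutes), first as patients might be hung-over", and also to limit reactivity to alcohol assessment, which it regards as a source of bias.

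**The concern.** A moderator has to be fixed before treatment. If it is measured afterwards, participants with high or low scores in one arm may not be the counterparts of those with the same scores in the other. A treatment-by-score interaction may then mix true moderation with an effect of treatment on the score. Here the protocol's own model places moderators ahead of the session, while the only trait score available is taken about a month after it.

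At stake is one Aim 3 interaction, and any moderated mediation that uses the same score. Aim 4 finalises the intervention model from the conclusions of the three preceding aims. A spurious finding that BMI works better or worse in highly reactant patients could therefore influence what is disseminated.

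**Working it through.** **1. Timing.** The relevant sections, side by side:

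| Item | Section | When |
|---|---|---|
| Demographics, AUDIT, Readiness Rulers | 9.3.1 E | Day 1, before randomisation |
| Session (BMI or brief advice) | 9.3.1 G | Day 1, after randomisation |
| Summary letter (BMI) | 6.1.2.1, 8.2.1 | After the session |
| First booster (BMI, if the participant agrees) | Synopsis, 6.1.2.1 / 8.2.1 | 1 week / 2 weeks |
| Trait reactance | 5.3, 9.3.2 | Month 1 only |

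The two booster timings contradict each other and must be reconciled. Both fall before month 1, so the ordering does not depend on which applies.

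**2. Missing scores.** Section 11.2 gives 172 per group, so N = 2 × 172 = 344, with 5-20% attrition over the follow-ups. Month-1 loss is not given separately.
- At 5%: 0.05 × 344 = 17.2, so about 17 missing and 327 scored.
- At 20%: 0.20 × 344 = 68.8, so about 69 missing and 275 scored.

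Month 1 is the earliest follow-up. If loss accumulates, the lower figure is the nearer one and 69 is an upper bound.

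**3. When the interaction is distorted.** Take a standardised baseline reactance R0, an outcome Y with unit variance within arm, correlation b between them in both arms, and no true moderation. The month-1 score equals R0 in the control arm. In the BMI arm:
- *Uniform shift*, R1 = R0 − s: the slope stays b, so the spurious interaction is 0.
- *Shrinkage*, R1 = (1 − c)R0: the slope becomes b/(1 − c), so the spurious interaction is bc/(1 − c). With b = 0.2 and c = 0.3: 0.06/0.7 = 0.086.
- *Tracking the outcome*, R1 = R0 + kY: the slope becomes (b + k)/(1 + 2kb + k²). With b = 0.2 and k = 0.3: 0.5/1.21 = 0.413, so the spurious interaction is 0.413 − 0.2 = 0.213.

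A simulation gave the rates below. It used 3,000 trials per row, 344 participants, a linear model with robust standard errors, a treatment effect of 0.25 SD, a nominal 5% test and 5% random loss unless stated. The simulation standard error at 5% is √(0.05 × 0.95/3000) = 0.4 percentage points.

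| Change in BMI-arm reactance | False positives, b = 0.2 | b = 0.3 |
|---|---|---|
| None | 4.8% | 5.9% |
| None, 20% random loss | 5.4% | 5.6% |
| Uniform shift, 0.3 SD | 5.2% | 5.6% |
| Shrinkage 20% | 7.8% | 9.9% |
| Shrinkage 30% | 10.6% | 15.7% |
| Shrinkage 30% plus shift 0.3 SD | 10.4% | 16.9% |
| Tracks outcome, k = 0.1 | 13.4% | 11.9% |
| Tracks outcome, k = 0.2 | 33.7% | 26.6% |
| Tracks outcome, k = 0.3 | 57.3% | 44.9% |

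The values of b, c, k and s are all assumptions; the protocol supplies none. The table shows which mechanisms matter, not what will happen in this trial. Contact at month 1 that depends on arm and reactance is a further route. It was not simulated and no size is attached to it.

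**The case against.** **Reactance is not named as a moderator, and the SAP may settle the list.** The list in 11.4.1 is illustrative and 5.3 does not separate moderators from mediators. So the link is an inference, though a natural one, because no other scale could stand for personality traits. The SAP could leave the score out, but it cannot supply a pre-treatment score that the visit schedule never collects.

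**A trait should be stable, and no change is documented.** This stands. The defect is that stability is taken for granted, not that it is known to fail.

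**The short baseline is deliberate.** This also stands. Section 7.2 gives two reasons for it, and keeping 14 items off an emergency-room questionnaire is a defensible trade-off.

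A reader might infer more than the documents support:
- *That the arms have opposite exposures on reactance.* Brief advice is described as clinician-led structured feedback, advice and referral. It is nowhere called confrontational, and 6.2.2 has both interventions presented alike to participants.
- *That every BMI participant has had a booster by then.* Boosters depend on agreement.
- *That any shift biases the test.* A uniform one does not.
- *That a confirmatory result is compromised.* Moderation is a secondary objective, and the protocol gives it no confirmatory status.

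**Conclusion.** The point holds, and it is minor. The plan tests treatment interactions with personality traits and places moderators before the session, yet its only trait score is taken after randomisation and treatment, and only in those reached at month 1. An interaction with that score cannot be presented as baseline moderation.

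Whether it would mislead cannot be derived from the protocol. Distortion needs an uneven change in reactance, a change in step with the outcome, or contact that depends on arm and reactance. Under the assumed values, the first two raise a 5% false-positive rate to about 8-17% and 12-57% respectively; a uniform shift or random loss leaves it at 5-6%. The conclusion rests on reading trait reactance as the scale meant by personality traits. The primary analysis and the Day-1 moderators are unaffected, and Aim 4 draws on more than this one interaction.

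**What to change.** State in 11.4.1 and 11.4.3 that claims of effect moderation rest on variables measured before randomisation. For month-1 reactance:
- report the mean, the spread and the number missing by arm (the spread matters, because a comparison of means alone would not reveal shrinkage);
- report any treatment-by-reactance interaction as descriptive;
- do not use it alone to tailor the model in Aim 4.

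This changes wording only. Its downside is that one exploratory moderator carries less interpretive weight. Similar spread and missingness in the two arms would be reassuring but would not exclude a change in step with the outcome.

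Measuring the scale on Day 1, before randomisation, would remove the problem. It is optional: it adds 14 items (roughly two minutes, assumed) to a baseline that 7.2 keeps at about 5 minutes and the synopsis puts at 5-10. That has to be weighed against hangover and assessment reactivity, the two reasons 7.2 gives for brevity.
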